#### *5.2.2 Elaboration on secondary outcomes*

The study is a feasibility trial only powered to answer the primary aim. However, we regard the above mentioned as important feasibility measures. The trial will include additional outcomes focused on hemodynamics, organ failure, and long-term outcomes in order to be able to power calculate for the planned large-scale trial.

Both 30-day and 90-day survival will be obtained from electronic medical records or the Danish Civil Personal Register which allows for accurate and virtually complete follow-up.

We will include 90-day survival as a measure of long-term survival. 90 days were chosen since it is unlikely that mortality later than that will be directly linked to the sepsis event or the trial interventions.

A vasopressor will be defined as any continuous infusion of noradrenaline, dopamine, dobutamine, terlipressin, vasopressin, phenylephrine, and/or adrenaline. Receiving vasopressors for a total of at least 3 hours on a given day is defined as receiving vasopressors for that day. Invasive ventilation is defined as mechanical ventilation through an endotracheal or tracheostomy tube, not only used for surgery for a total of at least 3 hours on a given day.

## **5.4 Safety and harm**

### *5.4.1 General consideration*

The trial will only be conducted in departments that are used to care for and treat sepsis patients. We therefore in general believe it is safe for individual patients to be enrolled into the REFACED Sepsis trial.

As described above, randomized trial data and data from observational and physiological studies do not provide firm evidence, that one of the interventions in the REFACED Sepsis trial is superior to the other. We therefore believe, that the REFACED Sepsis trial is safe for the patients also at the group level.

Generally, fluid administration is considered safe and is very commonly used in clinical practice. The overall benefit and potential harm will be captured in our secondary outcomes, and the clinical team will document any specific adverse events suspected to be related to the intervention.

The registration of the batch numbers and the expiry dates of the IV fluids and the identity of the clinician administering the fluid will be registered as per standard practice at the sites. These data will not be registered in the trial documents, but can be obtained by the Sponsor or the authorities if needed. We believe that this is a safe procedure because the IV fluids used in the REFACED Sepsis trial has been in clinical use for many years and the safety of single doses cannot be questioned. The same procedure was approved by the Danish Medicines Agency in the CLASSIC pilot trial (EudraCT no. 2014-000902-37) and the large-scaled CLASSIC trial (EudraCT no. 2018-000404-42).

The intervention arm in the present trial does not dictate which type of isotonic crystalloid that is to be used. SARs are defined from the Danish summaries of product characteristics of the most frequently used isotonic crystalloids in Denmark (normal saline (0.9% NaCl), Ringer-lactate, and Ringer-acetate). Participants in both intervention arms are expected to receive fluid resuscitation, but the amount is hypothesized to differ. The use of fluids has some obvious reactions presented in the Danish Summary Product Characteristics for the crystalloid solutions (see appendix 3+4).

#### *5.4.2 Definitions for adverse events and reactions*

The following definitions will be used:

Adverse event (AE): any untoward medical occurrence in a subject to whom a medicinal product is administered and which does not necessarily have a causal relationship with this treatment

Adverse reaction (AR): All untoward and unintended responses to an investigational medicinal product related to any dose administered

Serious adverse event (SAE): Any adverse event that results in death, is life-threatening, requires hospitalization or prolongation of existing hospitalization, results in persistent or significant disability or incapacity, or is a congenital anomaly or birth defect.

Serious adverse reaction (SAR): Any adverse reaction that results in death, is life-threatening, requires hospitalization or prolongation of existing hospitalization, results in persistent or significant disability or incapacity, or is a congenital anomaly or birth defect. The SARs are identified in the Danish Summary of Products Characteristics (SmPC) for the used crystalloids.

Suspected unexpected serious adverse reaction (SUSAR): a serious adverse reaction, the nature, severity or outcome of which is not consistent with the reference safety information (SmPC).

#### *5.4.3 Assessment of adverse events*

##### *Timing*

In all participants, we will assess the occurrence of SARs in the 7 days following randomization (the intervention period is 24 hours; 7 days allow for another 6 days of assessment after the intervention, which is clinically relevant in critically ill patients).

##### *Classification of an event*

We will make no inferences about a causal relationship between the intervention and the SARs but register the occurrence in the two groups and report them in the final report according to the definition given above. The investigators will classify SAEs (as per the definition above occurring within 7 days from randomization) and report them to the sponsor. If such a SAE is deemed both unexpected and related to the intervention by the investigator, it will be considered a SUSAR and reported as such. If the sponsor does not adjudicate the SAE as related to the intervention, this will also be noted in the final report to the Medicines Authorities.

#### *5.4.4 Definitions of serious adverse reactions in REFACED Sepsis*

Defined serious adverse reactions (SARs) are:

- General tonic-clonic seizures: Stiffening and/or jerking movements of all 4 extremities in a patient who becomes or is unconscious after randomization
- Anaphylactic reactions defined as urticarial skin reaction AND at least one of the following observed after randomization:
  - Worsened circulation (>20% decrease in systolic blood pressure or >20% increase in vasopressor dose)
  - Increased airway resistance (>20% increase in peak pressure on the ventilator) if intubated

- Clinical stridor or bronchospasm
- Subsequent treatment with bronchodilators
- Central pontine myelinolysis seen on CT or MRI scan within the 7-day after randomization
- Hyponatremia defined as P-Na > 159 mmol/L on any plasma sample including point-of-care testing after randomization if hyponatremia is not present at randomization or worsening of a preexisting hyponatremia with an increase in P-Na of > 5mmol/L from baseline (at enrollment)
- Severe hyperchloremic acidosis defined as pH < 7.15 AND p-chloride > 115 mmol/L on any plasma sample, including point-of-care testing after randomization if hyperchloremic acidosis is not present at randomization or worsening of a preexisting hyperchloremia with an increase in p-chloride > 5 mmol/L or decrease in pH > 0.05 (AND pH < 7.15 at baseline) from baseline (at enrollment)
- Severe metabolic alkalosis defined as pH > 7.59 AND SBE > 9mmol/L on any plasma sample, including point-of-care testing after randomization if metabolic alkalosis is not present at randomization or worsening of a preexisting metabolic alkalosis with a increase in pH > 0.05 and increase in SBE > 5mmol/L from baseline (at enrollment).

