#### **5.2 Secondary outcomes**

##### *5.2.1 Definitions*

The secondary outcomes will be

- Feasibility measures:
  - Number of patients with major protocol violations,

- Number of patients screened positive (ie.with all inclusion criteria fulfilled and no exclusion criteria fulfilled) vs randomized
- Time from admission to inclusion
- Number of patients lost to follow up in terms of 24-hour fluids (e.g. due to discharge within 24 hours)
- Accumulated serious adverse reactions and events (SAEs + SARs+ SUSARs) within 7 days in-hospital
- Total fluids (oral and intravenous) at 24 hours

We will also report in-hospital mortality and 30- and 90-day mortality (possible outcomes for the final large scale trial), in-hospital length of stay (LOS), mechanical ventilation within 7 days of admission (yes/no), vasopressor use within 7 days of admission (yes/no), and development or worsening of acute kidney failure according to the KDIGO3-criteria within 7 days of admission (also an SAE, see above) .

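### The worsening branch of the severe hyperchloremic acidosis SAR can be met, in a patient already hyperchloremic at baseline, without acidosis or while acidosis resolves

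*Protocol*

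**What the plan says.** Protocol section 5.4.4 gives the severe hyperchloremic acidosis item two branches. The new-event branch needs both abnormalities in a post-randomization sample: "pH < 7.15 AND p-chloride > 115 mmol/L on any plasma sample". The second branch covers patients who are already abnormal: "worsening of a preexisting hyperchloremia with an increase in p-chloride > 5 mmol/L or decrease in pH > 0.05". Directly after the pH change comes a parenthesis that adds, with a capitalized AND, a baseline pH below 7.15. Both changes are measured from enrollment. This branch sets no chloride cut-off for the pre-existing state and does not require acidosis to be part of it.

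The next item in the list, metabolic alkalosis, starts from the named condition itself and needs both changes: "worsening of a preexisting metabolic alkalosis with a increase in pH > 0.05 and increase in SBE > 5mmol/L".

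Section 5.4.2 defines a serious adverse reaction by its consequences: "Any adverse reaction that results in death, is life-threatening, requires hospitalization or prolongation of existing hospitalization", and so on. Section 5.4.3 describes the handling: "We will make no inferences about a causal relationship between the intervention and the SARs but register the occurrence in the two groups". Section 7.1.6 records each listed reaction as yes or no. The counts enter the secondary outcome in section 5.2.1, "Accumulated serious adverse reactions and events (SAEs + SARs+ SUSARs) within 7 days in-hospital", and section 5.4.6 sends a yearly list of all SARs to the medicines agency and the ethics committee.

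**The concern.** An item named for an acidosis should not be met by a patient who has none, or whose acidosis is clearing. The *or* between the two changes, the position of the parenthesis and the undefined starting state together allow this. Two abstractors could also classify the same patient differently, depending on how far they take the parenthesis to reach.

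This matters because the wording alone decides the count, and a chloride rise is a direct result of giving chloride-rich fluid. Section 5.4.1 says: "Participants in both intervention arms are expected to receive fluid resuscitation, but the amount is hypothesized to differ". A rule that scores a chloride shift as a serious reaction can therefore pick up part of the intended volume difference and report it as a safety difference, in a trial meant to inform a larger one.

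**Working it through.** **1. The wording as a decision rule.** The worsening branch gives no cut-off for hyperchloremia, so I take the item's own 115 mmol/L as an assumption. Three readings are possible:

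- A: the parenthesis qualifies the pH fall only (as printed).
- B: the parenthesis qualifies both changes.
- C: the item's leading thresholds (pH below 7.15, chloride above 115 in the later sample) govern the worsening branch too.

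| Chloride, mmol/L | pH | A | B | C |
|---|---|---|---|---|
| 104 to 112 | 7.40, stable | no | no | no |
| 108 to 118 | 7.40 to 7.38 | no | no | no |
| 116 to 122 | 7.40, stable | **SAR** | no | no |
| 116 to 122 | 7.25 to 7.38 | **SAR** | no | no |
| 116 to 122 | 7.10 to 7.30 | **SAR** | **SAR** | no |
| 116 to 117 | 7.10 to 7.02 | SAR | SAR | SAR |
| 116 to 122 | 7.10 to 7.02 | SAR | SAR | SAR |

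The bold entries are the misclassifications. Reading A gives three and reading B gives one, because B tests pH at baseline only. The first two rows show that a chloride rise above 5 mmol/L is never enough without hyperchloremia at baseline.

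**2. Direction between arms.** Section 6.1 supplies planned 24-hour volumes of 2650 and 1650 ml, SD 1.7 L in both arms. These are the inputs to its sample size, which reproduces: the two-sample t-test needs 61.7, so 62 per arm and 124 in total. The rest of this step is illustration under assumptions the protocol does not make: all fluid is 0.9% saline (9 g/L ÷ 58.44 g/mol = 154 mmol/L chloride), it mixes simply into an extracellular volume E, and none is excreted.

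Rise in chloride = (154 − Cl₀) × V ÷ (E + V).

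With Cl₀ = 116 and E = 14 L:

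- Standard arm mean: 38 × 2.65 ÷ 16.65 = 6.0 mmol/L.
- Restrictive arm mean: 38 × 1.65 ÷ 15.65 = 4.0 mmol/L.
- Volume at which the rise reaches 5: 5 × 14 ÷ (38 − 5) = 2.12 L.
- With normally distributed volumes, 62% of hyperchloremic standard-arm patients exceed this, against 39% in the restrictive arm.
- Standard-arm share of such events: 62 ÷ (62 + 39) = 61%.

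Over E = 10 to 18 L, Cl₀ = 110 to 120 and normal or lognormal volumes, the share is 57 to 70%. It moves towards 50% if lower-chloride crystalloids are used.

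**3. Possible count.** The protocol gives no prevalence of baseline hyperchloremia. If it were 1 to 10% (an assumption), 0.62 to 6.2 of the 62 patients per arm would be exposed to the rule. Under reading A and the model above, the total would be 62 × prevalence × (0.62 + 0.39), or about 0.6 to 6.3 events. The standard-arm excess would be 62 × prevalence × (0.62 − 0.39), or about 0.1 to 1.4 events. Leaving out excretion and assuming all saline push these figures up.

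**The case against.** The best defense is that the sentence should be read as a whole. The phrase tying the changes to baseline follows the parenthesis and must apply to both, so the parenthesis may be meant to apply to both as well. That is reading B, and it removes the normal-pH case. This part stands: the normal-pH result depends on the printed position of the parenthesis. But reading B still counts the patient whose pH recovers. Only reading C removes that case, and the worsening clause carries its own conditions rather than pointing back to the leading thresholds.

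A second defense is that the seriousness test in section 5.4.2 would screen out a bare laboratory shift. The protocol describes no step that applies it to the listed items, which are simply marked yes or no.

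Third, the sodium item also treats a single rise above 5 mmol/L as worsening. That item is defined by one variable, so one change suffices there. This one is defined by two.

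Fourth, each reaction type is recorded separately, so a reader of the results could isolate this component, and a broad safety definition is a cautious choice. The first part is fair and limits the harm. The second does not justify calling a normal pH a severe acidosis.

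A reader might also infer that any chloride rise above 5 mmol/L counts. It does not: hyperchloremia must already be present, and patients given 500 ml or more before randomization are excluded, so the group may be very small. Nor do the documents support saying that the average hyperchloremic standard-care patient would cross the line. At Cl₀ = 112 and E = 15 L the model gives 42 × 2.65 ÷ 17.65 = 6.3 mmol/L, but at Cl₀ = 116 and E = 18 L it gives 38 × 2.65 ÷ 20.65 = 4.9.

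**Conclusion.** The defect is in the text and holds under both ordinary readings. As printed, a patient with pre-existing hyperchloremia scores a severe hyperchloremic acidosis SAR on a chloride rise above 5 mmol/L at normal pH. With the parenthesis extended to both changes, a patient with baseline pH below 7.15 scores it while the acidosis resolves. Either result is at odds with the new-event branch and with the way the alkalosis item is built.

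The tendency towards the standard arm follows from the planned volumes if saline is used. Its size does not follow from anything in the protocol. One might infer that these events would fall mainly under standard care and distort the safety comparison. The documents do not carry that: the 57 to 70% share assumes all saline and no excretion, section 3.3.1 leaves crystalloid type free in the restrictive arm, and no rate of baseline hyperchloremia is given. The primary outcome and the sample size are unaffected. The point is worth correcting because it is cheap and because even a few misclassified serious reactions are visible in a trial of 124.

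**What to change.** Rewrite the worsening branch in section 5.4.4 so that it agrees with the item's own thresholds:

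- It applies only to patients with pH below 7.15 and chloride above 115 mmol/L at randomization.
- The post-randomization sample must still meet both thresholds.
- It must also show the stated change from baseline: chloride up by more than 5 mmol/L, or pH down by more than 0.05.
- All other patients are judged by the new-event branch.

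On the cases tabulated above this gives the column for reading C: the three misclassified patients drop out and both patients with deepening acidosis stay in. Copying the alkalosis item's *and* while keeping the baseline pH condition would also remove the three, but it would lose the patient whose pH falls from 7.10 to 7.02 with a chloride rise of only 1 mmol/L.

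Put the same wording in the data dictionary, and confirm that pH and chloride are captured at baseline and through day 7. Sections 7.1.5 and 7.1.6 mention blood gases but name neither value, and the daily list in section 7.1.7 names no laboratory values.

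The cost is one sentence in the protocol, a matching dictionary entry and, if they are not already captured, two laboratory fields. The downside is that fewer SARs will be counted, so the change should be fixed before the data by arm are reviewed.

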#### *5.4.5 Definitions of Suspected Unexpected Serious Adverse Reaction (SUSAR) in REFACED Sepsis*

SUSARs will be defined as serious reactions not described in the Summaries of Product Characteristics for the used crystalloids happening within 7 days of admission if not otherwise stated. Suspected Unexpected Serious Adverse Reactions (SUSAR) will be reported to the regulatory authorities as applicable.

#### *5.4.6 Reporting*

Any SAE adjudicated to be unexpected or related to the trial intervention by the investigator, will be reported within 24 hours to the sponsor or his delegate. If deemed a SUSAR by the sponsor, he will report it to the Danish Medicine Agency, the Ethics Committee and all trial sites within 7 days. No later than 8 days after the reporting, the Sponsor will inform the Danish Medicines Agency of relevant information on the Sponsor's and the investigator's follow-up action to the life-threatening or fatal SUSAR. Any other SUSARs will be reported to the Danish Medicines Agency no later than 15 days from the time when the Sponsor is informed.

In Appendix 3, SAEs seen frequently in critically ill sepsis patients are listed. The listed SAEs do not have to be reported to the sponsor within 24 hours of occurrence if judged not to be related to the intervention and

expected in the patient population in accordance with the flowchart. All SAEs not listed in Appendix 3 will be reported to sponsor within 24 hours of occurrence.

Once a year, the sponsor will submit a list of all SARs that have occurred at all sites during the trial period and a report on safety of the trial subjects to the Danish Medicines Agency and National Ethics Committee. The sponsor will notify and upload the results from the clinical trial including important adverse events on EudraCT using the “Declaration of the End of Trial Form” when the trial has been completed (no later than 90 days thereafter) and if earlier than planned, the reasons for stopping the trial.

## **6. SAMPLE SIZE CALCULATION AND STATISTICAL ANALYSIS PLAN**

### **6.1 Sample size calculation**

The trial will be powered to the primary outcome of 24-hour total intravenous fluids. Sample size calculation is based on unpublished data from an observational study conducted in three of the hospitals in Central Denmark Region. The study found that sepsis patients received a mean of 3762 ml (SD 1839) intravenous and oral fluid in 24 hours. Looking at only patients with sepsis, blood cultures drawn and intravenous antibiotics, patients received 2670 ml intravenous fluids (SD 1695). We conservatively estimate that the total amount of IV fluid in the control group will be approximately 2650 ml (standard deviation 1.7 L). We consider a mean difference of 1 L to be clinically meaningful and therefore estimate 1650 ml (standard deviation 1.7 L) in the intervention group. Based on these estimates, an alpha of 5%, a power of 90%, and a two-sample t-test, a sample size of 124 patients is required; 62 in each treatment arm. Using the same standard deviation of 1.7 L, which is even higher than the mean in the restrictive arm, is or most conservative estimate being able to segregate the two groups.

### **6.2 Statistical analysis plan**

#### *6.2.1 General considerations*

The statistical reporting will adhere to the CONSORT guidelines. All tests will be two-sided, a p-value < 0.05 will be considered significant, and all confidence intervals will have 95% coverage.

Patient inclusion and exclusion will be illustrated in a CONSORT flow diagram (see Appendix 7 for a draft).

We will include measures related to feasibility including the enrolled to screened ratio, time to randomization, and protocol adherence/major protocol violations. All analyses will be conducted in the intention-to-treat (ITT) population defined as all randomized participants for whom consent was obtained. We will perform the primary analyses adjusted for the stratification variable site.

The two groups will be compared in relation to baseline patient and sepsis characteristics using descriptive statistics.

#### *6.2.2 Primary and secondary outcomes*

To estimate the mean difference in fluid volume between groups, we will use linear regression with adjustment for the stratification variable. If the data is severely non-normally distributed, we will consider other appropriate options (e.g., "robust standard errors" or transformation). Other continuous variables will be analyzed similarly. For binary outcomes, we will use logistic regression adjusted for site and results will be presented as odds ratios.

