### *3.3.5 Criteria for modification of interventions for a given trial participant and protocol violations*

The clinical team may at any time violate the protocol if they find it to be in the interest of the participant. We will have a 24-hour per day trial hotline to enable discussion between the clinicians caring for trial participants and the REFACED Sepsis trial team regarding protocol related issues.

Protocol violations are defined as follows:

| Intervention group               | Major protocol violation                                                                                                                                                                                                                                                                                                                                                        | Documentation                      |
|----------------------------------|---------------------------------------------------------------------------------------------------------------------------------------------------------------------------------------------------------------------------------------------------------------------------------------------------------------------------------------------------------------------------------|------------------------------------|
| Restrictive fluid administration | IV fluids given if none of the bellow is true: 

• 1 or more hypoperfusion criteria fulfilled

• To correct documented fluid loss

• To correct significant electrolyte deficiencies

• Fluid administered as carrier for medication (e.g. antibiotics)

• Ensure a total fluid input of 1 L per 24 h

 | Reasons for the protocol violation |
| Standard care                    | No IV fluids given                                                                                                                                                                                                                                                                                                                                                              | Reasons for the protocol violation |

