### **4.2 Inclusion criteria**

The research team, clinically working nurses and ED physicians will screen ED patients for the following inclusion criteria:

- 1) Unplanned emergency department admission
- 2) Age  $\geq 18$  years
- 3) Sepsis defined as
  - a) suspected infection by the treating clinician AND
  - b) blood cultures drawn AND
  - c) IV antibiotics administered or planned AND
  - d) An infection related increase of SOFA-score  $\geq 2$  from baseline
- 4) Expected hospital stay > 24 hours as deemed by treating clinician

These broad inclusion criteria were chosen to investigate the effect of fluid administration in the entire, broad sepsis population and increase the likelihood of describing the entire 24 hours inclusion period. We will strive to enroll participants as soon as they fulfill the criteria in the ED. There is no exact maximum time frame for patient inclusion, however with the exclusion criteria of > 500 ml. IV fluids administered, the inclusion is expected and intended to happen within the first couple of hours.

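### The general odds-ratio rule in section 6.2.2 covers major protocol violations, which are a different event in each arm, so the contrast would not measure adherence

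*Protocol*

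**What the plan says.** Section 5.2.1 of the protocol lists "Number of patients with major protocol violations" first among the feasibility measures, which are secondary outcomes. Each patient either has a major violation or does not, so the outcome is binary.

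Section 6.2.2 is headed as covering the primary and secondary outcomes. Its rule for this type of outcome is: "For binary outcomes, we will use logistic regression adjusted for site and results will be presented as odds ratios". It neither names nor exempts any binary outcome.

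The table in section 3.3.5 (criteria for modification of interventions and protocol violations) defines the event by arm:

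- Restrictive arm: "IV fluids given if none of the bellow is true", followed by five permitted reasons. One of them is fluid that carries medication such as antibiotics.
- Standard care: "No IV fluids given".

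Section 6.2.1 says of feasibility: "We will include measures related to feasibility including the enrolled to screened ratio, time to randomization, and protocol adherence/major protocol violations". It does not say how these measures are to be analysed. The same section sets the general testing rule: "All tests will be two-sided, a p-value < 0.05 will be considered significant, and all confidence intervals will have 95% coverage".

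**The concern.** An odds ratio between arms is meaningful when the same event is counted in both. Here the restrictive arm counts fluid given when it should not have been, and the standard arm counts fluid not given at all. The model's null hypothesis would be that these two unrelated probabilities are equal, which is not the hypothesis that the two regimens were followed equally well. Neither adjustment for site nor a larger sample changes that.

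This is a feasibility trial, and sections 1.3 and 9.1 make a later large trial depend on its result. How well clinicians kept to the restrictive regimen is a figure that the planners of that trial will want. An odds ratio would hide it behind a comparison that has no adherence interpretation, and in some datasets the odds ratio could not be reported at all.

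**Working it through.** **Inputs from the protocol.** 62 patients per arm and two-sided alpha 0.05 (sections 6.1 and 6.2.1). The two violation definitions are in section 3.3.5. Every patient must have "IV antibiotics administered or planned AND" the other parts of the sepsis definition (section 4.2). The expected standard-care volume is 2650 ml (section 6.1). No violation rate is given for either arm, so every rate below is an assumption.

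**The plan's own figure.** For a difference of 1000 ml, SD 1700 ml, 90% power and a two-sample t-test, the exact calculation gives 61.7 per arm. That rounds up to 62 per arm, 124 in total, with power 90.1%. The stated sample size reproduces, and nothing below alters it.

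**Step 1: the null hypothesis.** Write pR for the probability of IV fluid without a permitted reason in the restrictive arm, and pS for the probability of no IV fluid in standard care. The logistic model tests

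pR/(1 − pR) = pS/(1 − pS), that is, pR = pS.

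The two sides refer to different events, so equality does not mean equal adherence and inequality does not mean unequal adherence.

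**Step 2: the standard-arm event should be rare.** IV antibiotics are given or planned for everyone, and the table in section 3.3.5 treats medication carrier as a form of IV fluid. Standard care has no upper limit and follows the clinician's choice (section 3.3.2). If carrier fluid counts, a standard-care patient with no IV fluid over 24 hours would be unusual.

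**Step 3: estimability.** The chance of no standard-arm event among 62 patients is (1 − pS)^62:

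| Assumed pS | Chance of zero events |
|---|---|
| 1% | 0.99^62 = 54% |
| 2% | 0.98^62 = 29% |
| 5% | 0.95^62 = 4% |

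With zero events there and at least one in the restrictive arm, the maximum-likelihood odds ratio is infinite.

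**Step 4: can a rejection probability be given?** The table shows exact enumeration over all outcomes at 62 per arm, without the site term. A zero cell counts as non-rejection for the Wald test.

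| Restrictive vs standard (assumed) | Fisher | Likelihood ratio | Wald |
|---|---|---|---|
| 5% vs 1% | 5% | 36% | below 1% |
| 10% vs 0% | 60% | 96% | 0% |
| 10% vs 1% | 42% | 74% | 11% |
| 10% vs 3% | 20% | 41% | 13% |
| 15% vs 1% | 79% | 93% | 32% |

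The answer runs from near 0% to near 100%, depending on the assumed rates and on a choice of test that section 6.2.2 does not make. No single figure is supportable.

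**Step 5: what a usable result looks like.** With 6 restrictive-arm violations, 6/62 = 9.7%, and the exact (Clopper-Pearson) 95% interval is 3.6% to 19.9%. This is directly readable as adherence to the restrictive regimen.

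**The case against.** The strongest reply is that nobody plans this odds ratio. Section 6.2.2 does not name violations. Section 6.2.1 treats feasibility measures in a sentence of their own that mentions no test. One of those measures, screened versus randomized, cannot have an arm-wise odds ratio, because patients who are not randomized have no arm. Descriptive reporting is therefore a natural reading. Section 12 also promises a methodology article with the statistical analysis plan.

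Part of this stands: the odds ratio follows from an unqualified general rule and is not an explicit plan for violations. But section 6.2.1 says only that these measures will be included. Where it intends description alone, for baseline characteristics, it says so. The rule in 6.2.2 is already fixed in this protocol and, followed as written, covers the outcome.

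A reader might go further and infer that the test would come out significant against the restrictive arm because of the definitions, even if clinicians departed from both regimens equally often. The documents do not support that. They give no violation rates, and standard care leaves the volume to the clinician, so there is little fixed regimen to override. Under a Wald test, a zero standard-arm count leads to a non-estimable result and not to significance.

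It is also fair to say that no decision rule rests on this odds ratio. Section 2 defines feasibility by the reduction in IV fluid volume, and section 5.2.2 says that the trial is powered only for the primary aim.

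The companion sentence in 6.2.2 on other continuous variables would likewise cover "Time from admission to inclusion". That interval is essentially settled before allocation, so comparing arms on it would be uninformative but would bias nothing. It is not part of this point.

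**Conclusion.** The point holds as a minor one. Read as written, section 6.2.2 assigns a between-arm odds ratio to an outcome whose event differs by arm. Any such result, significant or not, could not be read as a comparison of adherence. This follows from the definitions alone and needs no assumed rate.

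The second part, that the odds ratio may not be estimable, does rest on assumptions: that medication carrier counts as IV fluid when the standard-arm definition is applied, and that the standard-arm rate is therefore low. At 1%, 54% of trials would have no standard-arm event; at 5%, only 4% would.

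No claim is made about how often the test would reject. The primary outcome, its analysis and the total of 124 patients are untouched.

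**What to change.** Add to section 6.2.2 that major protocol violations are reported separately by arm as n/N with an exact 95% confidence interval, without an odds ratio or p-value, and that the restrictive-arm proportion is the adherence result.

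This takes a sentence or two, needs no new data and changes no other analysis. The only thing given up is a between-arm p-value for violations, which would have had no interpretation as a difference in adherence.
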